#### 2.3.2. Process Measures

Data on process indicators, contextual measures and subjective experience measures were collected by interviews, focus group discussions, and document analysis.

We aimed to interview one school principal, one at-school Jump-in coordinator, two teachers, six to eight parents and six to eight children per school, as well as the health promotion professional supporting that school. The interviews were planned around the T_1_ measurements, approximately 12 months after the start of the implementation of the intervention on dietary habits. Interviews and focus group discussions were held in Dutch and done by two researchers. One of the researchers led the interview or focus group discussion, the other researcher kept track of time and took minutes. We aimed to interview a diverse population of teachers (i.e., based upon gender, grade they educate), parents (i.e., gender, age of child), and children (i.e., gender, age). In order to facilitate recruitment of parents and children for the process evaluation, the schools’ Jump-in coordinator advised which approach would suit best to optimise participation in focus group discussions. An example was planning the discussions on a Wednesday morning because more parents are free from work. When parents and children signed up for the focus group discussion, they received a confirmation by e-mail or phone. If we were not able to recruit enough participants for a focus group discussion, we conducted a group interview. If schools didn’t participate during the first follow-up measurement, they participated during the second follow-up measurement.

*Interviews.* Semi-structured interviews were held to assess the process indicators (e.g., reach), contextual factors and satisfaction with the programme. These interviews were held with the health promotion professional, school principal, at-school Jump-in coordinator and teachers. Measured items in the interview guides were based on the topic lists used in the Jump-in physical activity study and DOiT study [21,43] and was built up according to the implementation process from Fleuren et al. [29]. An example of a question regarding process indicators included: “How many components of the Jump-in healthy nutrition policy have been implemented in this schools’ nutrition policy?” Examples regarding the implementation process were: “How and who decided to participate in the Jump-in programme?”, “Which factors hampered the implementation of the healthy nutrition policy at this school?” and “which factors hamper or facilitate a long-term implementation of this healthy nutrition policy at this school?” An example of a question regarding the innovation strategies was: “How many workshops took place?”

*Focus group discussions.* Focus group discussions were held to assess the contextual factors regarding the user and socio-political characteristics, innovation strategies and satisfaction with the programme. We conducted focus group discussions with parents and children. Items in the checklist were based on De Meij et al. [21] and van Nassau et al. [43]. In the focus group discussion with parents, we used different statements and sticky notes to discuss characteristics of the socio-political context (e.g., financial consequences of the intervention), innovation context (e.g., clarity of procedures), and innovation strategies (e.g., communication regarding the intervention). In the focus group discussion with children we used drawings and sticky notes to discuss the characteristics of the socio-political context (e.g., norm at home), the innovation context (e.g., clarity of procedures), and the innovation strategies (e.g., workshops).

*Document analysis*. Document analysis was included to assess process indicators, contextual factors and satisfaction. These documents comprised of Jump-in scan logs of effect data collection and interview notes. Jump-in scans are structured, uniform logs kept by the health promotion professionals to keep track of when which intervention components are implemented. It serves as an instrument to structure and aid the quality of intervention delivery and implementation. Furthermore, the logs of the effect evaluation data collection allowed us to monitor potential effect evaluation measurement flaws.

### 2.4. Analyses

#### 2.4.1. Quantitative Analysis

Prior to data collection, we estimated that 107 subjects for each cohort was needed (d = 0.5, SD = 1.0, α = 0.05, power 80%) in order to detect a statistical difference between our control (i.e., T_0_) and intervention groups (i.e., T_1_ and T_2_). Assuming each class consisted of a minimum of 25 students, five schools were required. When we took into account the cluster design and possible non-response, we took a sample that consisted of twice the number of schools needed [44]; hence, the sample size was ten primary schools.

We will conduct a series of multilevel regression analyses. This analysis takes into account different clusters (i.e., class level, potentially school level). Same-age data from different time points and cohorts will be compared, in which cohorts consist of a group of children from the same age from all ten participating schools. We will create a variable for at-school consumption by combining the food and drinks consumed in the first and second school break, i.e., sugar-sweetened beverages, water or tea without sugar, milk, whole wheat bread, fruit, vegetables, snacks consumed at school. This will be done based on the parent and child questionnaires, and the photographs. Behavioural determinants (attitude, knowledge, social norm, modelling, physical environment, liking and habit formation) will be derived from the parent and child questionnaires.

To analyse the effect of the intervention on the combined scores of at-school dietary behaviour and behavioural determinants, we will use multilevel regression analyses. For continuous outcome variables we will use linear multilevel regression models with time point as first level variable and grade as second level variable. When variables are not normally distributed, we will use Poisson multilevel analysis. For categorical variables we will use logistic multilevel models. To examine whether observations cluster at school level, we will add schools as third level in the linear models. If this is the case, schools will be added to all models—creating a three-level structure—and for categorical variables we will shift to a GEE analysis.

To explore the moderation effects by SEP, age in years, sex and ethnicity, we will add interaction terms to the model. When these terms are significant, we will stratify the analyses for these specific subgroups.

Finally, to study whether children compensate for at-school dietary changes when they are home, we will adjust at-school child dietary behaviour for at-home child dietary behaviour (i.e., combined score of consumption in the morning and after school, derived from the parent and child questionnaire). A significance level of *p* = 0.05 will be used and *p* = 0.10 for moderation effects. For the analyses we will use IBM SPSS Statistics Version 21.0 (IBM, Armonk, NY, USA) and STATA/IC 15.1 (StataCorp LLC., College Station, TX, USA).

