#### 2.1.2. Effect Evaluation

The Extended Selection Cohorts (ESC) design entails a cohort-longitudinal design with adjacent cohorts [25], that are measured at two or more time points [26]. Each cohort represents an age cohort including subjects of approximately the same age.

In our study, each cohort—represented by school grades—was measured three times: at baseline, 12 and 24 months after baseline measurements. Each cohort at follow-up was compared to the same-age adjacent baseline cohort group (see Figure 1). For instance, the measures of 2-year exposed cohort 3 (grade 5 in 2018–2019) were compared to the measures of 1-year exposed cohort 4 (grade 5 in 2017–2018) and to baseline measurements of cohort 5 (grade 5 in 2016–2017).

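### The main model's stated levels (time point, grade) conflict with the promised class clustering and leave the class of a given school year, and the repeatedly measured child, unmodelled

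*Protocol article*

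**What the plan says.** Section 2.4.1 of the protocol article introduces the multilevel analysis with "This analysis takes into account different clusters (i.e., class level, potentially school level". Two paragraphs later it gives the operative model for continuous outcomes: "linear multilevel regression models with time point as first level variable and grade as second level variable". Of schools it says "To examine whether observations cluster at school level, we will add schools as third level in the linear models"; if clustering is found, school joins all models, and "for categorical variables we will shift to a GEE analysis". The clustering unit of that GEE is not named. In the same section, "cohorts consist of a group of children from the same age from all ten participating schools".

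Section 2.1.2 says the design "entails a cohort-longitudinal design with adjacent cohorts" and that each cohort "was measured three times: at baseline, 12 and 24 months after baseline measurements". The comparison is: "Each cohort at follow-up was compared to the same-age adjacent baseline cohort group". No sentence names the child as a level or cluster.

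**The concern.** The two descriptions in section 2.4.1 do not define the same model. Time point separates control (T0) from intervention (T1, T2), so it is the effect to be estimated and belongs in the fixed part; it can index level-1 records only if these are nested in something, and no child level is given. Grade is the factor on which cohorts are matched. Neither is the class of a given school year: the children who share a room, a teacher and that year's application of the nutrition policy.

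The article states that the design cannot control for time trends, so T1 and T2 against T0 is the only quantitative evidence of effect. An analyst who follows the level sentence literally would attach standard errors to that contrast that omit class-by-year variation and the repeated measurement of children. The Poisson and logistic models would presumably inherit the same levels.

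**Working it through.** **Inputs.** From the article: ten schools, at least 25 pupils per class (2.4.1), three waves (2.1.2), child questionnaires in grades 5–8 and photographs in all grades (2.3.1). The plan's own step 107/25 = 4.28, rounded up to 5 schools, reproduces and implies one class per grade per school; the 107 itself plays no part here. Assumed, because the article gives none: class ICC 0.02, 0.05 or 0.10; within-child correlation ρ = 0.4; total variance 1; equal classes; complete data.

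**Step 1: which levels reach the time contrast.**
- Grade over all schools, grade within school, and school each contain T0, T1 and T2 data. A random intercept at any of them largely cancels from T2 − T0.
- A class (school × grade × year) exists at one wave only, so its effect does not cancel. It is not a stated level.
- A child appears at several waves, but in a different grade each time. It is not a stated level.

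**Step 2: class omitted, class effect wholly year-specific.** Take grades 3–8: 60 classes and 1,500 children per wave.
- True variance of T2 − T0 = 2 × [ICC/60 + (1 − ICC)/1500] = (2/1500) × (1 + 24 × ICC).
- Model variance = 2/1500.
- True SE / model SE = √(1 + 24 × ICC); the number of grades drops out.
- ICC 0.02: √1.48 = 1.22. ICC 0.05: √2.20 = 1.48. ICC 0.10: √3.40 = 1.84.
- Type I error = 2 × [1 − Φ(1.96/ratio)] = about 11%, 19% and 29%.

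**Step 3: half of the class effect stable over years.** Read grade as grade within school, so that its intercept absorbs the stable half.
- True variance ∝ 25 × ICC/2 + 1 − ICC; model variance ∝ about 1 − ICC/2.
- √(1.230/0.990) = 1.11; √(1.575/0.975) = 1.27; √(2.150/0.950) = 1.50.
- Type I error about 8%, 12% and 19%.

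**Step 4: child omitted, no class effect.** By the example in section 2.1.2, grade 5 is cohort 5 at T0, cohort 4 at T1 and cohort 3 at T2. A single-grade contrast therefore compares different children: factor 1.00. If grades are pooled and a fraction f of cohorts appears at both waves, true SE / model SE = √(1 − f × ρ).
- Grades 5–8: T0 is cohorts 5–8 and T2 is cohorts 3–6, so f = 2/4; √0.80 = 0.894, and the model SE is 1/0.894 = 1.12 times the true one.
- Grades 3–8: T0 is cohorts 3–8 and T2 is cohorts 1–6, so f = 4/6; √0.733 = 0.856, and the model SE is 1.17 times the true one.

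**Step 5: both omitted, grades pooled, T2 against T0.**
- Class effect wholly year-specific, grades 3–8: √(1 + 24 × ICC − 0.267) = 1.10, 1.39 and 1.77 (type I error about 8%, 16% and 27%).
- Class effect travelling with the cohort, ICC 0.05 and ρ = 0.4, from the full covariance matrix with grade effects in the model: 1.17 for grades 5–8 and 0.98 for grades 1–8.

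**The case against.** The best defence is that the level sentence is loose wording. Class clustering is promised explicitly. The statement about all ten schools defines cohorts, not the grade level. A grade spanning all schools could not nest within school as a third level, whereas grade within school can, and the sample-size step implies one class per grade per school. On that reading grade is the class, and time point at level 1 merely means the individual record. The described contrast also compares different children, the two omissions pull in opposite directions, and no correlation is documented. Finally, this is a condensed article, and the random-effects detail may sit in an analysis plan that is not shown.

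Much of this stands. A reader might infer that the class is simply not a cluster, or that the standard errors are shown to be wrong by a known amount. The article supports neither: class is named in one sentence, and size and net direction depend on unstated correlations. Nor does taking grade as random rather than fixed do much harm in a balanced layout, where every grade appears equally at each wave.

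What does not stand is that reading grade as grade within school repairs the model. That unit still pools three school years and different children, so its intercept mostly cancels from the time contrast, and class-by-year variation stays in the residual (step 3). A GEE clustered on school with robust variance would cover both class and child, but the clustering unit is not named, it applies only to categorical outcomes and only if school clustering is found, and ten clusters are few. Nor is this a detail merely left for later: the article fixes the levels, in a form that conflicts with its own preceding statement.

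**Conclusion.** The concern holds in a limited form. Section 2.4.1 gives two incompatible level structures, and under either reading of grade the specified one has no level for class-by-year or for child. If classes vary from year to year, standard errors for T1 and T2 against T0 are too small: by a factor of about 1.22 to 1.84 for an assumed, wholly year-specific ICC of 0.02 to 0.10 with 25 per class, and by less if part of the class effect is stable or travels with the cohort. Omitting the child changes nothing in a single-grade contrast. With pooled grades and an assumed correlation of 0.4 it makes the T2 standard error about 12% (grades 5–8) to 17% (grades 3–8) too large. Across the combined cases worked here, the net ratio runs from 0.98 to 1.77. The article does not say whether grades are pooled or whether records can be linked across waves, so no single corrected figure can be given. The structure should be settled before the models are fitted.

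**What to change.** Replace the level sentence in section 2.4.1 with one structure that applies to the linear, count and logistic models:
- time point (T0, T1, T2) and grade as fixed categorical factors;
- random intercepts for class, defined as school × grade × school year, and for school;
- where grades are pooled and records can be linked, a child random intercept crossed with class, since children change class-year at each wave.

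If records cannot be linked, keep class and school and state that repeated children are not modelled. Say whether grades are pooled, and name the clustering unit if GEE is retained.

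The cost is analysis wording and computing time, with no new data. Cross-classified models take longer to fit and may need simplifying for the count and categorical outcomes; the order of simplification should be stated in advance.

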To assess children’s dietary behaviour, children, parents and teachers filled in questionnaires and we photographed the food and drinks children brought to school at T_0_, T_1_ and T_2_. The executive researcher and research assistant conducted the measurements with support from health promotion professionals and MSc students. In all grades children’s lunchboxes were photographed. In addition, children in grade 5–8 filled in questionnaires which was aided by the research team when a question was unclear. Data collection followed a few logistical considerations: (1) data collection was conducted before 10 AM (school breaks usually take place at 10 AM), (2) data collection was not conducted on Mondays in grades 5–8 (to avoid that children reported on weekend days), (3) data collection at fruit days was avoided (i.e., Dutch schools can sign up for the EU schoolfruit project in which they receive free fruits/vegetables a few days a week for 20 weeks), and (4) short schooldays were avoided. The children received a questionnaire for their parents in an envelope to take home. A few days before the deadline to hand in the questionnaire, the parents received a reminder to fill in the questionnaire. Prior to the start of Jump-in, health promotion professionals made agreements with schools ensuring the schools’ involvement with the programme and introduced the evaluation study. Subsequently, the coordinating researcher explained in detail what the study entailed including the required time investment. After each data collection wave schools received an incentive and a factsheet illustrating the percentages of drinks and foods consumed by the pupils. Additionally, the existing relationship between the health promotion professional and the school facilitated optimal compliance to the study protocol. Completed parent questionnaires were returned to the school and collected by the teacher. After data collection, the questionnaires were scanned. The food groups depicted on the photographs were entered in a Microsoft Access database by one the researchers. Categorising products to certain food groups and specifying the quantities was done based on an established Dutch Food Composition Database [34]. In the Netherlands, lunch boxes, packages and sipping cups have a standardized size, which gave us an indication of the quantity of the products consumed by children. Beverages are usually offered in 0.21 (e.g., packages of sugar-sweetened beverages), 0.2751 (e.g., sipping cups) or 0.51 (e.g., water bottles) packages. Bread usually has a standardised size as well, which enabled us to count the number of slices of bread. Portions of fruits and vegetables were counted based on the guidelines from the Dutch Food Composition Database. For instance, two mandarins are classified as one portion of fruit and five cherry tomatoes as one portion of vegetables. Last, we counted the number of snacks, which were usually packed per portion. After processing the photographs, a second researcher checked congruence. When dissonance between interpretation of food groups or quantities occurred, a third researcher checked these photographs and disagreement was discussed until consensus was reached.

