
*Questionnaires.* At-school and at-home dietary habits were assessed using questionnaires for parents and 8–12 year old children, and through short questionnaires for teachers. Questionnaires for parents and children comprised of three parts. First, the consumption of water or tea without sugar, milk, sugar-sweetened beverages, whole wheat bread, fruit, vegetables and snacks was asked using an adapted 24-h recall method. The parent questionnaire additionally comprised an adapted food frequency questionnaire (FFQ). Questions regarding the determinants of children’s dietary behaviour included attitude, social norm and modelling with regard to parents and peers, physical environment, liking and dietary habits, using 5-point Likert scales with smileys. These smileys were added to the scales because visual stimulation aids children’s motivation to fill in a questionnaire [35,36]. Third, socio-demographic characteristics of the target population were asked [37].

*Pre-test Questionnaires.* Prior to data collection, relevant questions from the validated ENERGY questionnaires were selected to assess the dietary habits regarding the dietary outcome measures [38,39]. The questionnaires were supplemented with relevant questions from the ProChildren study (assessing fruit and vegetable consumption) [40,41] and ChecKid [42]. If necessary, questions were slightly adapted in consultation with experts. Questionnaires were pretested among children and parents, and the order was based according to the moment of the day rather than by product group to increase the questionnaire’s comprehensibility. Then questionnaires were pre-tested at an after school-care facility to examine face validity with the target group (i.e., children and parents from families of ethnic minority groups and/or low SEP in disadvantaged areas of Amsterdam). This led to small adaptations to further improve the understanding of the questions and increasing the fun of filling out the questionnaire.

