To address both these issues, we included photographs of children’s at-school food and drinks. This method is not prone to self-reported recall bias, and—compared to questionnaires—is less time consuming, labour intensive and costly. However, it can be questioned whether it is prone to social desirability, e.g., when children hide unhealthy foods or drinks during data collection, or are not honest about the content of covered products (i.e., due to hygiene reasons we did not unfold products wrapped in tinfoil).

Furthermore, this method measures the products children bring to school without knowing whether they actually consume it. Photographs might not be suitable to accurately assess quantity. However, in the present study, we were specifically interested in whether the intervention enabled a shift towards healthier alternatives (e.g., a shift from sugar-sweetened beverages to water). For this objective, photographs can be useful.

Although not extensively researched yet, some authors found that digital imaging is a reliable alternative method for measuring fruit and vegetable intake during school lunch [52]. The use of both questionnaires and photographs to measure dietary intake in our research allows us to assess the effect of the intervention and compare both methods.

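### Sending every non-normal variable to a Poisson model selects on the wrong property; for 5-point Likert determinants it would make model-based standard errors too large

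*Protocol article*

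**What the plan says.** Section 2.4.1 (Quantitative Analysis) covers diet scores and determinants together: "To analyse the effect of the intervention on the combined scores of at-school dietary behaviour and behavioural determinants, we will use multilevel regression analyses". The model is then chosen in three steps. First: "For continuous outcome variables we will use linear multilevel regression models with time point as first level variable and grade as second level variable". Next: "When variables are not normally distributed, we will use Poisson multilevel analysis". Last, categorical variables go to multilevel logistic models. If observations cluster by school, a third level is added, and only the categorical variables move to GEE.

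Section 2.3.1 (Effect Measures) describes the outcomes that meet this rule:

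- Determinants from the questionnaires were asked "using 5-point Likert scales with smileys".
- From the photographs, bread has a standard size, "which enabled us to count the number of slices of bread". Fruit and vegetable portions were also counted, and "we counted the number of snacks, which were usually packed per portion".
- Drinks are described by package size: "0.21 (e.g., packages of sugar-sweetened beverages), 0.2751 (e.g., sipping cups) or 0.51 (e.g., water bottles) packages". The final 1 in each figure appears to be a misread litre symbol.

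The article gives no mean or variance for any outcome. It does not say whether drinks are analysed as volumes, packages or yes/no, or whether SEs are model-based or robust.

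**The concern.** The only trigger for the Poisson model is that a variable is not normally distributed. That property does not identify a count. It is also the wrong property to check: a linear model needs approximately normal residuals, and with about a hundred children per group a comparison of means tolerates some departure even there.

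A Poisson model with model-based SEs sets the variance equal to the mean, given the random effects. A bounded 1-5 score usually has a variance well below its mean, so its SE is overstated and a real change in attitude, liking or social norm can be missed. A null result on determinants could then come from the model. For true counts the risk runs the other way: if they are overdispersed within classes, the SE is understated and false positives increase.

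**Working it through.** **The plan's own figure.** The document attaches no number to the Poisson rule. The only computed figure nearby is 107 subjects per cohort (d = 0.5, SD = 1.0, α = 0.05, power 80%). A standard two-sided two-mean calculation with those inputs gives 63 per group, so 107 does not reproduce. That is a separate matter. Here 107 serves only as a group size.

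**Formulas.** With mean m and variance v, the model-based Poisson SE divided by the true SE is r = √(m/v). The true two-sided type I error at nominal 5% is 2·[1 − Φ(1.96·r)]. Power against a standardised difference d with n per group is about Φ(d·√(n/2) − 1.96·r). At d = 0.5 and n = 107, d·√(n/2) = 0.5·√53.5 = 3.657. With a correct SE (r = 1), power is Φ(3.657 − 1.96) = 95.5%. Clustering is ignored in these formulas.

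**Likert scores, bound without a distribution.** For a score coded 1 to 5, v cannot exceed (m − 1)(5 − m). This is below m when m² − 5m + 5 > 0, that is for m above (5 + √5)/2 = 3.62 (or below 1.38). There the Poisson SE is too large whatever the distribution.

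**Likert scores, assumed distributions (not from the document).**

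| Assumption | m | v | r | Power, d = 0.5, n = 107 |
|---|---|---|---|---|
| Uniform over 1-5 | 3.00 | 2.00 | 1.22 | 89.6% |
| Skewed (5/8/17/30/40%) | 3.92 | 1.33 | 1.71 | Φ(3.657 − 3.36) = 62% |
| Ceiling (2/3/10/25/60%) | 4.38 | 0.86 | 2.26 | Φ(3.657 − 4.44) = 22% |
| Mean 4.2, SD 0.8 | 4.20 | 0.64 | 2.56 | Φ(3.657 − 5.02) = 9% |
| Mean of four independent skewed items | 3.92 | 0.33 | 3.43 | 0.1% |

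For the 4.2/0.8 case, dividing 3.657 by 2.56 and treating the statistic as having unit variance gives Φ(1.43 − 1.96) = 30%. That is too high, because an inflated SE also shrinks the spread of the test statistic. The type I error is 0.016 for the uniform item and about 0.001 or less for the others.

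**Counts.** A true Poisson count gives r = 1 and type I error 5%. If v = 2m (assumed), r = 1/√2 = 0.707 and the type I error is 2·[1 − Φ(1.386)] = 16.6%.

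**Drinks, only if analysed as volume.** Assume 0, 0.2, 0.275 and 0.5 litre with shares 40/30/15/15%. In litres m = 0.176, v = 0.0298 and r = 2.43. Multiplying the unit by c divides r by √c, so r = 0.77 in decilitres and 0.077 in millilitres. The type I error is below 0.001, 0.13 and 0.88 for the same data.

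**Does the multilevel structure repair it?** A random-intercept Poisson model was simulated with 20 classes of 11 over 200 runs. For the skewed Likert item the empirical SE was 0.047 against a model SE of 0.068, with type I error 0.01. The model SE is what a plain Poisson model gives, √(2/(110 × 3.92)) = 0.068, so the random intercept changed nothing. For decilitres the SEs were 0.169 and 0.152, with type I error 0.095.

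**Do robust SEs repair it?** With the same estimate and a sandwich SE (107 per group, 1000 runs, single level), type I error was 0.04 to 0.06 for every outcome simulated.

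**The case against.** A reader might infer that the trial's SEs will be wrong in both directions. The document does not support that. It gives no dispersion and does not say that SEs are model-based. Robust SEs and dispersion checks may stand in a fuller plan, and their absence from an article is no finding. This stands, and the sizes above are conditional on model-based SEs.

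A reader might also infer that drink volumes go into the Poisson model, so that the p-value depends on the unit. No section says so. Drinks may be analysed as packages or yes/no, and the Discussion plays down quantity: "we were specifically interested in whether the intervention enabled a shift towards healthier alternatives". The unit argument is only a conditional warning.

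Nor is it shown that the rule will apply to almost every outcome. Slices, portions and snacks are counts, for which a count model is reasonable. Single Likert items might be classed as categorical and go to logistic models, although the article does not say so and analyses determinants alongside combined scores.

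The magnitudes depend on the inputs. Ten schools with one class of 25 give 250 per grade before clustering and non-response. Then 0.5·√125 = 5.59, and power is Φ(5.59 − 3.36) = 99% for the skewed item and Φ(5.59 − 5.02) = 72% for mean 4.2, SD 0.8. The loss can therefore be much smaller than at 107. The single-level formulas also overlook that class effects absorb overdispersion between classes, so the 17% applies only to excess variance within classes.

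None of this defends the trigger. The rule is stated, not omitted, and the GEE switch does not reach the Poisson models.

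**Conclusion.** The concern holds as a criticism of a badly fixed rule: the model is chosen by non-normality when it should be chosen by type of outcome. The firmest consequence is for Likert determinants analysed as continuous scores. With model-based SEs and 1-5 coding, the SE is too large for every mean above 3.62, and under the assumed distributions it is 1.2 to 3.4 times too large. The error for realistic Likert scores is conservative: power is lost and type I error is not inflated. SEs that are too small arise only for counts overdispersed within classes, or for volumes in small units if volumes are analysed at all. The document establishes neither. The criticism of the wording is secure; the numbers are illustrations. It should be fixed before analysis, but it does not invalidate the design.

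**What to change.** Replace the sentence in section 2.4.1 with a rule by outcome type:

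- Counts (slices, portions, snacks): negative binomial, or Poisson with cluster-robust SEs.
- Likert determinants: linear multilevel with robust or bootstrap SEs, or ordinal logistic.
- Any outcome analysed as a volume: linear with robust SEs.
- Yes/no outcomes: logistic, as already planned.
- Normality: judged on model residuals, not on the raw variable.

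The text should also say which class each outcome belongs to, in particular Likert items and drinks. Recasting all photograph and recall products as present/absent would suit the stated interest in a shift between products, but it changes the outcome definition and is not needed to cure this defect.

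The cost is a change of wording and slightly more analysis work. No new data are required.
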